# DATA HANDLING AND ANALYSIS

**Data analysis plan, including statistical methodology and planned tables and figures**

SAS 9.1 (Cary, NC) as well as the WHO drug efficacy tools provided at <http://www.who.int/malaria/toolsformonitoring.html> will be used for data management and analysis. Data will be analyzed using two methods: **per protocol analysis**, where patients who were withdrawn from the study or who were lost to follow-up are excluded, and **survival analysis**, where all enrolled patients are included in the analysis until the last day before drop-out. In addition to voluntary withdrawals or treatment non-compliance, patients will be considered for the analysis as withdrawn if the PCR results are unclassifiable.

The final analysis will include:

- A description of the patients screened, and the distribution of the reasons for exclusion.
- A description of the patients included in the study.
- The proportion of patients lost to follow-up or withdrawn and the distribution of reasons for withdrawal.
- The PCR-adjusted and unadjusted proportion of ETF, LCF, LPF, and ACPR in the Pf arm at day 28 and day 42 with 95% confidence intervals using both methods of analysis.
- Both drug-level and PCR-adjusted and unadjusted proportion of treatment failures in each Pv arm at day 28 and day 42 with 95% confidence intervals using both methods of analysis
- Frequency of side effects, severe malaria, anemia, and hospitalizations by treatment arm

**Data collection**: Data will be collected and recorded at the health facility by one of the trained staff members. All data entry forms will be checked for completeness. Laboratorians may complete brief reports on laboratory findings to share with clinicians who will transfer these results to the case report form of the appropriate patient, the laboratory results will be entered into an Excel database.

**Information management and analysis software:** Microsoft Excel (Redmond, Washington) will be used for double entry of laboratory data and clinical data. SAS 9.1 (Cary, NC) will be used for data analysis.

**Data entry, editing, handling, storage and disposition**: Some open-ended data including the names of specific drugs or diagnoses will be coded prior to data entry. A list of standard codes for these fields will be developed by hand once collection of data is complete. All forms will then be coded and checked by 2 different team members.

Data will be double entered using Microsoft Excel (Redmond, Washington). Systematic routines will be developed to check for data entry discrepancies and range and consistency. All discrepancies will be resolved by reference to the original checked data collection forms. The final data set will be transformed to SAS for analysis and will no longer contain any personal identifying information.

Original data collection forms will be handled only by staff members and kept under locked storage until completely coded, checked and transported for data entry. Once data entry and cleaning are complete the original forms will be stored under lock and key at ICAP until final analyses and reports have been prepared. They will then be destroyed.

**Storage of specimens**:Specimens obtained in this study will be saved only for the duration of molecular testing and drug testing of treatment failures and then destroyed. No samples will be stored. Specimens will not be tested for HIV.

**Quality control/ assurance**: Site supervisors will check data collection forms at the end of follow-up for completeness and accuracy of recording.

**Bias in data collection, measurement and analysis**: Some bias may be introduced through the fact that both treating clinicians and parents will be aware of which treatment a subject received; as much as possible we will rely on objective measures of improvement (fever resolution, malaria parasitemia) which will be unaffected by knowing the treatment allocation. In addition, the microscopists reading the slides will be blinded to the treatment allocation. Other biases in data collection will be minimized by use of standardized data collection instruments.

**Intermediate reviews**: Although this study aims to study the efficacy of accepted and widely used first-line treatments in Ethiopia, a data safety monitoring board (DSMB) consisting of members not involved in the study will be set up to protect the rights and welfare of the subjects. The objectives, accountability, responsibilities, membership, and procedures of the DSMB are detailed in Annex VIII.

**Limitations**: Results from this study may not be applicable to other ACTs or other areas of Africa with different resistance patterns. In addition, the nature of *in vivo* drug efficacy studies always involves some compromise between statistical power, representativeness, and practical logistic constraints. Therefore the study will not be powered to estimate differences in efficacy across treatment arms or between sites. The three health facilities were not chosen randomly and thus may not be representative of our target population.

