5. After assignment, on day 0, each patient will receive the morning dose of treatment medication under direct observation and will be monitored for vomiting. The patient or parent will be given the evening dose (for AL only) to administer at home. Each patient will return on days 1 and 2 for subsequent doses. Clinical reassessments will be made on days 1- 3, 7, 14, 21, 28, 35, and 42 (see Annex V for a table of scheduled procedures). Participants will be given 35 Ethiopian Birr for each visit to cover their travel expenses (this is enough to cover round-trip transportation by bus to the clinic for one adult; parent traveling with the enrolled child requiring their own seat (age >6 years) will receive 50 Birr). Patients will be advised to return on *any* day during the follow-up period if symptoms return and not to wait for scheduled visit days. Patients who do not present to the facility for follow-up visits will be followed at home. This is standard for in vivo studies based on the WHO protocol, but is not the standard for routine care. Typically, for patients not enrolled in a study, the parent would be given all the doses of the medicine to administer at home, and no follow-up would be scheduled. The parent would be told to return if the child did not improve.

6. Blood films (thick and thin) for parasite count will be obtained and examined at each visit except day 1 and on any other day if the patient spontaneously returns with fever or worsening symptoms. Hemoglobin status will be measured on days 0, 7, 14, 21, 28, 35, and 42. A filter paper blood spot will be collected on days 0 and in case of treatment failure. All molecular testing will be conducted in Addis Ababa, Ethiopia, by Ethiopia Health and Nutrition Research Institute (EHNRI). Blood drug level testing capacity does not currently exist in Ethiopia and will be conducted at CDC Atlanta. All samples will have the study ID number and date of collection, but no other personal identifiers. The logbook that links the study ID number to the patient will be kept at the study site locked in a cabinet when not in use during the study enrollment period. After the completion of the study, this logbook will be stored in a locked cabinet in Addis Ababa at the International Center for AIDS Care and Treatment Program’s office.

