### ANNEX V Schedule of follow-up activities

|  | day 0 | day 1 | day 2 | day 3 | day 7 | day 14 | day 21 | day 28 | day 35 | day 42 |
| --- | --- | --- | --- | --- | --- | --- | --- | --- | --- | --- |
| PROCEDURES |  |  |  |  |  |  |  |  |  |  |
| Clinical assessment | X | X | X | X | X | X | X | X | X | X |
| Temperature | X | X | X | X | X | X | X | X | X | X |
| Blood slide for parasites count | X | (X) | X | X | X | X | X | X | X | X |
| Hemoglobin | X |  |  |  | X | X | X | X | X | X |
| Filter paper | X | (X) | (X) | (X) | (X) | (X) | (X) | (X) | (X) | (X) |
| TREATMENT |  |  |  |  |  |  |  |  |  |  |
| Drug to be given | X | X | X |  |  |  |  |  |  |  |
| Rescue treatment |  | (X) | (X) | (X) | (X) | (X) | (X) | (X) | (X) | (X) |

**NOTES:** Parentheses denote conditional or optional activities. On Day 1, the patient should be examined for parasitemia if she or he has any danger sign. Rescue treatment could be given on any day, provided that the patient meets the criteria for treatment failure. Extra days are any days other than regularly scheduled follow-up days when the patient returns to the facility because of recurrence of symptoms. On extra days, blood slides may or may not be routinely taken. Filter paper collection forPCR will be taken on day 0 and on day of treatment failure.

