**Any other day:**

Clinical assessment — referral in case of severe malaria/danger signs

Measurement of axillary temperature

Parasitological assessment

Hemoglobin/hematocrit if indicated clinically

Alternative treatment in case of treatment failure

Optional: blood sampling for PCR

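### The rule that counts unclassifiable PCR as withdrawal is not limited to the PCR-adjusted estimates; applied as written, it removes or censors known failures in the unadjusted ones

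*Protocol*

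**What the plan says.** The data analysis plan in the protocol (Data Handling and Analysis) names two methods. The per protocol analysis is one "where patients who were withdrawn from the study or who were lost to follow-up are excluded". The survival analysis is one "where all enrolled patients are included in the analysis until the last day before drop-out". Directly afterwards it adds that "patients will be considered for the analysis as withdrawn if the PCR results are unclassifiable". No type of estimate is named in that rule.

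The list of final analyses then asks for "The PCR-adjusted and unadjusted proportion of ETF, LCF, LPF, and ACPR in the Pf arm at day 28 and day 42" and for "Both drug-level and PCR-adjusted and unadjusted proportion of treatment failures in each Pv arm at day 28 and day 42". Both items are to be produced with 95% confidence intervals by both methods.

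On sampling, Enrollment Procedures (item 6) states: "A filter paper blood spot will be collected on days 0 and in case of treatment failure". The notes to Annex V agree that filter paper for PCR "will be taken on day 0 and on day of treatment failure". Annex VI, under the heading for any other day, lists "Optional: blood sampling for PCR".

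The End-points section and Annexes I and II define failure for both species from parasitemia, temperature or fever history, danger signs and hospitalization. None of these definitions refers to a genotype.

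**The concern.** The unadjusted failure proportion does not need PCR. It counts recurrent parasitemia that meets the failure definition, whatever its source, and so should not depend on how well the laboratory work goes. A withdrawal rule triggered by a PCR result undoes that if it reaches the unadjusted estimate.

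The effect runs one way. A patient who completes follow-up without recurrence has no follow-up sample to classify and cannot be removed by this rule. A patient who fails can be. Per protocol, that patient leaves both numerator and denominator. In the survival analysis, the failure event turns into a censoring. Either way the drug looks better than the observed data show.

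These proportions are the study's primary outcome. The protocol says they will inform national treatment policy, including whether one drug should be used for both species.

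**Working it through.** **Step 1: the plan's own figure.** The sample size section assumes an ACPR of 90%, 120 patients per arm and 20% loss to follow-up, and gives an exact 95% interval of 82.4% to 95.1%. The Clopper-Pearson interval for 90 successes in 100 is 82.38% to 95.10%, so the figure reproduces with 100 evaluable. Literal use of 20% loss gives 120 × 0.8 = 96 evaluable. I use 96 and check 100 below.

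**Step 2: who the rule can reach.**
- Follow-up sample: at treatment failure only (Enrollment Procedures; Annex V notes).
- Purpose of PCR: to sort recurrences by origin (End-points).
- Failure status: settled without PCR (End-points; Annexes I and II).

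So any patient with an unclassifiable pair of samples already counts as a failure in the unadjusted outcome.

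**Step 3: per protocol effect.** With n evaluable, f failures and k of those unclassifiable:
- all failures kept: f/n
- rule applied: (f − k)/(n − k)
- understatement: f/n − (f − k)/(n − k) = k(n − f)/[n(n − k)], which is positive whenever k > 0 and f < n.

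The protocol gives no value for k. I assume 10%, 20% and 30% of recurrences, and f = 10 to match the planned 10% failure. With n = 96:
- k = 0: 10/96 = 10.4% (ACPR 89.6%, exact 95% interval 81.7% to 94.9%)
- k = 1: 9/95 = 9.5%
- k = 2: 8/94 = 8.5%
- k = 3: 7/93 = 7.5% (ACPR 92.5%, interval 85.1% to 96.9%)

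The understatement is 0.9, 1.9 and 2.9 points. With n = 100, the same counts take 10.0% to 9/99 = 9.1%, 8/98 = 8.2% and 7/97 = 7.2%, so the choice of 96 or 100 is immaterial.

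**Step 4: survival effect.** Assume 96 patients and recurrences of 3, 3 and 4 on days 28, 35 and 42, with no other losses.
- All kept as events: (93/96) × (90/93) × (86/90) = 0.896, so failure is 10.4%.
- One unclassifiable patient censored just before each of the three days: (93/95) × (90/92) × (86/89) = 0.925, so failure is 7.5%.

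Censoring loses about as much as exclusion does.

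**The case against.** The strongest reply is that the authors meant only the PCR-adjusted estimate. The trigger is a PCR result, an unadjusted estimate does not use one, and the plan lists adjusted and unadjusted results separately. A reader might infer from the unrestricted wording that the authors decided to drop these patients everywhere. The document does not establish that intention. What stands is that the sentence has no limit, that the estimates listed after it include unadjusted ones by both methods, and that no other section keeps these patients as failures. An analyst who follows the text would remove them.

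Three further inferences are tempting and should not be drawn.

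- *That the PCR-adjusted estimate is also biased downward.* The direction there depends on what the unclassifiable cases are. If they are recrudescences, leaving them out lowers failure. If they are new infections, leaving them out does not change the proportion or raises it, depending on how classified new infections are counted. Exclusion or censoring is defensible in that analysis.
- *That Annex VI leaves failures without a PCR sample.* Its optional sampling covers all unscheduled visits, including those without failure, while Enrollment Procedures and Annex V call for a sample at failure. The rule also speaks of unclassifiable results, and a sample never collected is not clearly the same thing. This is wording to reconcile, not evidence of lost data.
- *That the bias is much larger in vivax because no primaquine is given.* The understatement does grow with the number of recurrences, but the protocol gives no figure for a high recurrence rate. It cites failure of at most 5% and plans on 10%.

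Two mitigations are fair. Several markers plus microsatellites are planned for each species, which should limit unclassifiable results. The plan also promises the distribution of reasons for withdrawal, so a careful reader could restore these patients to the per protocol proportion. Restoring them to the survival curve would also need their recurrence dates. Neither mitigation corrects the reported estimates.

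**Conclusion.** The point holds for the unadjusted estimates. As written, the rule removes known failures from the per protocol proportion and censors them in the survival analysis, so unadjusted failure can only be understated. The direction follows from the protocol's own sampling and failure definitions and needs no outside assumption.

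The size does need one. At the planned failure rate, with 10% to 30% of recurrences assumed unclassifiable, the understatement is about 1 to 3 points on 10.4%. If none is unclassifiable, there is no error. Even the largest of these shifts keeps the ACPR (92.5%) inside the planned interval of 82.4% to 95.1%. Unlike sampling error, though, it always favours the drug. The conclusion does not extend to the PCR-adjusted estimates.

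**What to change.** - In the data analysis plan, state that patients with unclassifiable PCR are treated as withdrawn in the PCR-adjusted estimates only.
- Add that in every unadjusted estimate, per protocol and survival, a recurrence that meets the failure definition counts as a failure on the day it occurs, whatever the PCR result.
- Report the number of unclassifiable results per arm.
- Reconcile the optional PCR sampling in Annex VI with Enrollment Procedures and Annex V, which call for a sample at treatment failure.

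The handling of unclassifiable cases in the PCR-adjusted analysis may stay as it is. Bounds that count them all as recrudescence and then all as new infection would be informative there but are optional.

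The cost is one or two clarifying sentences, one reported count per arm and an aligned annex entry. No new data or patients are needed.

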# SUMMARY

Following the rapid development of significant drug resistance of *Plasmodium falciparum* (Pf) to chloroquine and then sulfadoxine-pyrimethamine (the first line therapy in Ethiopia 1998-2004), artemether- lumefantrine (Coartem or AL) was adopted as first line therapy in Ethiopia in 2004. According to the current national malaria diagnosis and treatment guidelines, first-line treatment for uncomplicated falciparum infection is AL. First-line treatment for *Plasmodium vivax* (Pv) is with chloroquine (CQ) alone without primaquine therapy in malarious areas. For all clinical infection without laboratory confirmation, AL which is effective against both Pf and Pv is the first-line treatment. Thus, in Ethiopia, where treatment for malaria without laboratory confirmation occurs frequently, Pv is often treated with AL as the standard of care. Furthermore, World Health Organization (WHO) recommends AL for the treatment of Pv, where AL has been adopted as first-line treatment for Pf. Now with wide-spread use of AL and CQ, we propose to conduct an antimalarial efficacy study to monitor the effectiveness of these therapies in Ethiopia and to determine how efficacious these drugs remain. This information will inform future policy changes with respect to appropriate antimalarial strategies.

The simplest and most universally accepted measure of testing for antimalarial drug treatment efficacy, the standardized procedures outlined in the World Health Organization *Assessment and monitoring of antimalarial drug efficacy for the treatment of uncomplicated falciparum malaria* and the WHO *Monitoring antimalarial drug resistance*, will be followed.

In this proposal, patients aged above 6 months with symptomatic malaria presenting to health centers will be enrolled for treatment with AL for *P. falciparum* infection, and either AL or CQ for *P. vivax* infection. Clinical, parasitologic, and hematologic parameters will be monitored for *P. falciparum* and *P. vivax* infection over a 42-day follow-up period, which will be used to evaluate drug efficacy. Results from this research study will be used to assist Ethiopia in assessing their current national malaria drug policies.

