# INTRODUCTION

The impact of malaria on the health and economic development of human populations is greatest in the tropics and sub-tropics [1]. The World Health Organization (WHO) has estimated 247 million cases of malaria and 881 000 deaths occurred in 2006 making it one of the world's leading killers [2]. Children under 5 years of age living in sub-Saharan Africa account for the majority of the illness and death caused by malaria worldwide. There are substantially less data on individuals 5 years of age and above.

Most countries in sub-Saharan Africa have adopted the WHO Global Strategy for Malaria Control, which relies primarily on prompt and effective antimalarial treatment. The ultimate success of this strategy rests on the ability of governments to provide antimalarial drugs which are indeed efficacious. Because of wide-spread and intensifying antimalarial drug resistance to a variety of currently available antimalarial drugs, the decision of which drug to recommend becomes both critical and complex.

Drug efficacy assessment methodology appropriate to the situation existing in sub-Saharan Africa has been developed over the last 20 to 25 years. The goals of these studies are to assess antimalarials currently being used for the treatment of uncomplicated malaria. These data are critical for guiding the development of rational antimalarial drug policies and treatment guidelines. The duration of the resolution of symptoms, the proportion of patients experiencing a “clinical failure” within a pre-determined follow-up period, and the ability of anemic patients to improve their hematologic status have become the primary indicators of antimalarial drug efficacy [3].

This document presents a standardized protocol for assessing the therapeutic efficacy of antimalarial drugs in Africa utilizing the most current concepts of not only what data are needed to accurately judge antimalarial efficacy, but also what information is required by national decision makers to devise rational policies and guidelines for their countries. This protocol is based on experiences gained in drug efficacy testing in numerous countries throughout the world and follows a standardized WHO protocol for drug efficacy testing [4, 5].

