# OBJECTIVES

To assess the therapeutic efficacy of AL for uncomplicated *P. falciparum* and *P. vivax* infections and chloroquine for *P. vivax* infection based on parasitologic, clinical, and hematologic parameters, we will conduct an open-label one-arm in-vivo efficacy assessment for *P. falciparum* and two-arm for *P. vivax*.

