**Rescue Treatment**

Patients failing in any arm will be treated with quinine 10mg/kg/dose every 8 hours for 7 days as per National Guidelines [24]. This treatment will be administered orally unless the patient has persistent vomiting, in which case he/she will receive IM/IV therapy until able to tolerate oral therapy.

**Concomitant Treatment** Using standard clinic procedures, clinic personnel will administer supportive treatment to patients as necessary:

- **Antipyretics** will be given for temperatures > 39oC as per national policy. All patients enrolled in the study will be given two additional doses of paracetamol for use at home. Patients/parents/guardians should be instructed in the use and application of tepid sponging and fanning as per national policy.
- **Ferrous Sulfate/ Folate** will be given to all children with hemoglobin <10 mg/dl as per Integrated Management of Childhood Illness (IMCI) Guidelines
- **Anti-helminthics** will be given to children with hemoglobin <10 mg/dl over one year of age as per IMCI Guidelines

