**Day 3, Day 7, Day 14, Day 21, Day 28, Day 35, and Day 42:**

Clinical assessment — referral in case of severe malaria/danger signs

Measurement of axillary temperature

Parasitological assessment

Alternative treatment in case of treatment failure

Hemoglobin/hematocrit (Day 7, Day 14, Day 28, Day 42), filter paper sampling for PCR in case of treatment failure

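### Efficacy is to be judged partly on hematologic parameters, but no hematologic endpoint is defined, and the one listed output, anemia frequency by arm, is not tied to day 0

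*Protocol*

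**What the plan says.** **Aim.** The Objectives section of the protocol says efficacy will be assessed "based on parasitologic, clinical, and hematologic parameters". The Summary says that clinical, parasitologic and hematologic parameters are followed "over a 42-day follow-up period, which will be used to evaluate drug efficacy". As background, the Introduction says that "the ability of anemic patients to improve their hematologic status have become the primary indicators of antimalarial drug efficacy", alongside symptom resolution and clinical failure.

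**Data.** Enrollment Procedures, item 6: "Hemoglobin status will be measured on days 0, 7, 14, 21, 28, 35, and 42". Annex V shows the same days. Annex VI gives a shorter list of follow-up days: "Hemoglobin/hematocrit (Day 7, Day 14, Day 28, Day 42", without days 21 and 35.

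**Endpoints.** The Specific Objectives, the End-points section and Annexes I and II classify outcomes on parasitemia, temperature and clinical course. None contains a hemoglobin measure.

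**Analysis.** The one hematologic item in the final analysis list is "Frequency of side effects, severe malaria, anemia, and hospitalizations by treatment arm".

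**Entry and co-treatment.** The anemia exclusion is hemoglobin below 5 g/dl. Under Concomitant Treatment, ferrous sulfate/folate "will be given to all children with hemoglobin <10 mg/dl as per Integrated Management of Childhood Illness (IMCI) Guidelines". Anthelmintics for children over one year use the same printed threshold.

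**The concern.** The protocol states an aim that its own analysis list does not clearly serve. A hematologic response to treatment is a change from a starting value, or recovery in those who started anemic. The list offers instead a frequency of anemia grouped with side effects, severe malaria and hospitalizations. Patients with hemoglobin of 5 g/dl or more can enter, so that frequency may combine three groups: anemic at entry and still anemic, newly anemic, and, depending on how it is counted, anemic at entry but since recovered.

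At stake is whether the trial can report on the hematologic part of its objective. The *P. falciparum* arm is the most exposed, because it has no comparator and day 0 is its only internal reference. In children, iron/folate and anthelmintics further blur what can be attributed to the antimalarial.

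**Working it through.** The plan gives no figure on this point: no anemia prevalence, recovery rate or incidence, and no hemoglobin input to the sample size. The check is therefore a reading of the sections side by side, plus an illustration on assumed rates.

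**1. Specification within the same list.** The *P. falciparum* and *P. vivax* efficacy items each name day 28 and day 42, 95% confidence intervals and both analysis methods. The anemia item names none of these, nor a cut-off, a baseline rule or a measure of change.

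**2. What an anemia frequency could mean.** Let p be the proportion anemic on day 0, r the proportion of those who recover by day 42, and i the proportion of the rest who become anemic (all assumed).

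- Ever anemic, day 0 included: E = p + (1 − p)i
- Anemic at day 42: V = p(1 − r) + (1 − p)i

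With i = 0 and r = 20%, 50%, 80%:

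- p = 10%: E = 10% throughout; V = 8%, 5%, 2%
- p = 30%: E = 30% throughout; V = 24%, 15%, 6%
- p = 50%: E = 50% throughout; V = 40%, 25%, 10%

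An ever-anemic count does not respond to recovery. A day-42 count does. The protocol does not say which is meant.

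**3. A day-42 count still does not identify recovery.** With i = 5%:

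- p = 30%, r = 80%: 0.30 × 0.20 + 0.70 × 0.05 = 0.060 + 0.035 = 9.5%
- p = 10%, r = 50%: 0.10 × 0.50 + 0.90 × 0.05 = 0.050 + 0.045 = 9.5%

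The frequency is the same, with recovery of 80% in one case and 50% in the other. Splitting by day-0 status separates them.

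**4. Share of the day-42 count that was present at entry**, with r = 60% and i = 3%:

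- p = 20%: 8.0% + 2.4% = 10.4%, of which 77% was present at entry
- p = 30%: 12.0% + 2.1% = 14.1%, of which 85%
- p = 40%: 16.0% + 1.8% = 17.8%, of which 90%

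**5. Chance imbalance between the vivax arms.** At 35% anemic and 120 per arm, the standard error of the baseline difference is √(2 × 0.35 × 0.65 / 120) = 6.2 points. A 10-point imbalance in either direction is 10/6.2 = 1.6 standard errors, about one chance in ten. By step 4, 30% against 40% at baseline shifts the day-42 figure by 17.8 − 14.1 = 3.7 points. The 95% half-width for that difference is 1.96 × √[(0.141 × 0.859 + 0.178 × 0.822)/n], which is 9.3 points at n = 120 and 10.3 at n = 96. The shift lies well within sampling noise.

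**6. Precision of a recovery analysis.** With 20% loss, 120 × 0.8 = 96 per arm. At p = 10%, 30% and 50%, about 10, 29 and 48 patients per arm are anemic on day 0. With 29 patients and 50% recovering, the approximate 95% half-width is 1.96 × √(0.25/29) = 18 points.

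**7. Internal contradictions.** Hemoglobin on days 21 and 35 is in Enrollment Procedures and Annex V but not in Annex VI. Concomitant Treatment prints its threshold in mg/dl. The exclusion criteria, Enrollment Procedures and Emergency Care use g/dl. Taken literally, 10 mg/dl is 0.01 g/dl, below the 5 g/dl entry limit.

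**The case against.** A reader might go further and infer that the planned frequency counts patients anemic at entry whatever the drug does, and so cannot show recovery or a drug effect. The documents do not support that. The analysis list fixes no time window. A table by visit would show prevalence falling (24% to 6% in step 2), and the randomized vivax arms are balanced at baseline in expectation. Nor would a baseline imbalance readily pass for a drug effect: no between-arm test is listed, the Limitations paragraph says the study is not powered for arm differences, and the illustrated shift is within noise.

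Three further points have weight. Cut-off, visit and baseline adjustment are often left to a statistical analysis plan, which may exist, and the list is not closed: it also includes a description of enrolled patients, where day-0 hemoglobin could appear. The Introduction's sentence on anemic patients describes how the field developed and does not set this trial's endpoints. The End-points section and the position of the anemia line suggest that it was meant as safety.

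These points limit the finding but do not remove it. The Summary and Objectives still claim hematologic efficacy, no section defines it, and the section that sets out the planned analyses gives only a frequency not tied to day 0.

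**Conclusion.** The concern holds as a mismatch within the protocol: hematologic parameters are part of the stated efficacy assessment, serial hemoglobin from day 0 is collected, no hematologic endpoint is defined, and the only listed output does not separate anemia at entry from persisting or new anemia. It answers the hematologic objective poorly, most clearly in the single *P. falciparum* arm.

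The consequence is secondary, because the primary parasitological and clinical results are unaffected. The true size cannot be derived: every prevalence, recovery and incidence figure above is an assumption. The illustrations show only that the listed frequency is ambiguous and, on most readings, dominated by anemia present at entry. The differences in hemoglobin days and units are plain contradictions on the page. They do not affect an analysis at days 28 and 42, which appear in all three schedules.

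**What to change.** In the final analysis list, replace the word anemia with three descriptive items by arm:

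- hemoglobin change from day 0 to days 28 and 42, adjusted for day-0 hemoglobin when the vivax arms are compared;
- recovery among patients anemic on day 0;
- new anemia among patients not anemic on day 0.

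State the anemia cut-off used for these tables. Report iron/folate and anthelmintic use alongside. Do not exclude treated patients: treatment is triggered by low hemoglobin, so excluding them would select on the outcome variable.

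Alternatively, remove hematologic parameters from the efficacy objective (and the matching Summary sentence) and label the anemia line as safety.

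In either case, the sponsor must reconcile the hemoglobin days in Annex VI with Enrollment Procedures and Annex V, and the hemoglobin unit under Concomitant Treatment with the exclusion criteria, Enrollment Procedures and Emergency Care.

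The analysis change costs a few table rows from data already collected, and the rest is text correction. Days 28 and 42 are in every schedule, so the new tables need no added procedure.
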